10^. A lack of antenatal diagnosis, delivery outside a tertiary paediatric surgery centre, and inadequate pre-hospital management and transfer results in significant delays in reaching care, during which time the bowel is exposed, contaminated, damaged and/ or torted on the vascular pedicle resulting in postnatal ischaemia and necrosis
^1,
6,
7,
12^. In addition, neonates commonly arrive hypovolaemic, hypothermic and septic
^6,
7,
11,
44^. In HICs, complex gastroschisis is associated with a significantly higher mortality at 17% compared to 2% for simple gastroschisis
^50^. In LMICs, the additional systemic compromise results in the majority of neonates with gastroschisis (both simple and complex) dying within a median of 4-days at a healthcare facility
^6,
7,
44^.

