### Current practice and guidelines

There are a number of components to successful gastroschisis management including: antenatal diagnosis, delivery in a tertiary paediatric surgery centre or adequate pre-hospital management and transfer, pre-intervention resuscitation, bowel reduction and defect closure, and post-intervention neonatal care including provision of parenteral nutrition (PN) until enteral feeding is established. In HICs, practically all neonates are diagnosed antenatally and a delivery plan is constructed resulting in either delivery at a tertiary paediatric surgery centre or rapid stabilisation and transfer to such a unit
^51^. Even in HICs, the latter has been shown to result in poorer outcomes
^52^. Methods of bowel reduction and defect closure vary widely
^53^. The two most commonly utilised techniques are primary closure in an operating room (OR) or cotside application of a preformed silo (PFS) with serial reductions over several days followed by cotside sutureless closure or closure in the OR
^54–
56^. Neonates are managed in an intensive care unit (ICU) by a multi-disciplinary team (MDT) of neonatologists, paediatric surgeons, anaesthetists, specialist nurses, and sometimes paediatric gastroenterologists. Ventilation is available if required and all neonates receive central intravenous (IV) access and PN. For neonates with simple gastroschisis the median duration of PN is 23-days and length of hospital stay (LOS) 36-days
^4^. Earlier time to first enteral feed has been associated with a shorter duration of PN and LOS in both HIC and LMIC settings
^31,
57,
58^.

In LMICs, many women do receive antenatal care as per World Health Organisation (WHO) guidelines; however, these do not include an ultrasound scan, which is required to detect congenital anomalies
^59–
64^. In a prospective cohort study of 42 neonates with gastroschisis in Uganda, 24% of mothers underwent a second trimester ultrasound by a technician holding a diploma
^6^. However, just one had a correct antenatal diagnosis and therefore over 95% were born outside of a tertiary paediatric surgery centre
^6–
8^. In this study, 81% were born in a first or second level healthcare facility, but appropriate care was not instigated; 81% were without appropriate bowel coverage, 54% without IV access, 83% without an nasogastric (NG) tube, 52% were breastfeeding, and only 58% arrived within 12-hours of delivery
^6^. Only 35% travelled by ambulance

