### Outline of the interventional bundle

The interventional bundle will consist of both pre-hospital and in-hospital components. Each of these will have core components that will be consistent across the seven study centres and adaptable components for optimisation to the local context (
Table 1). The content and detail of the core and adaptable components will be further defined utilising the results of the systematic review, qualitative study and Delphi process. A summary of the drivers to achieving a reduction in gastroschisis mortality is summarised in
Supplementary File 1
^110^.

**Table 1. T1:** An outline of the core and adaptable components of the interventional bundle.

Pre-Hospital	In-Hospital
Core	
A pre-hospital management protocol will be implemented at first and second level healthcare facilities (both government and private) that refer patients with gastroschisis to the study centres. These will be identified by the study leads at each site. The protocol will include: • Covering the bowel in clear plastic • Administering intravenous (IV) fluids • Keeping the neonate warm • Transferring to the study centre as soon as possible	• Use of a standardised protocol for care. • Neonatal resuscitation and ward care including IV access, IV fluids, maintenance of normothermia, appropriate antibiotics, regular monitoring and infection control. • Gastroschisis reduction and sutureless closure using a preformed silo, or equivalent, and avoidance of neonatal anaesthesia and surgery. • Early establishment of breastfeeding and enhanced enteral feeding programme.
Adaptable	

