## Data analysis

### Clinical outcomes

***Pre-post study analysis.*** Primary and secondary clinical outcomes will be compared pre- and post-intervention using chi-squared analysis for categorical variables or Fisher’s exact test if either of the groups contains less than 10 patients. For normally distributed continuous variables an unpaired t-test will be used and for non-normally distributed continuous variables a Mann-Whitney
*U* test will be used. P<0.05 will be deemed significant. Cases presenting during the 1-month implementation phase will be deemed post-intervention since the PI will be in attendance at all cases alongside the local team to assist with implementation of the protocol and training will have commenced.

***Time series analysis.*** Time series analysis will be undertaken using Statistical Process Control to distinguish significant trends and shifts in mortality from background variation during the study period
^134^.

***Multivariate analysis.*** Multivariate logistic regression analysis will be used to identify factors affecting all-cause in-hospital mortality with adjustment for confounding factors. Potential confounders include gestational age, weight, presence of co-morbidities, and ASA score at the time of primary intervention.

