### Study impact

The systematic review, qualitative study and Delphi process will all provide unique evidence towards optimising care for neonates with gastroschisis in low-resource settings. Each study will be submitted for publication. The interventional study will allow for that evidence to be tested in-practice across seven tertiary paediatric surgery centres in sub-Saharan Africa. The study design will enable detailed analysis of which components of the interventional bundle and implementation strategy were and were not effective. Including multiple sites in the study will determine the generalisability of the intervention and will permit a more detailed analysis of contextual factors affecting outcome.

If successful, funding will be sought to scale-up the intervention to other sites across sub-Saharan Africa and then LMICs globally using a stepped-wedge approach. This has the potential to save the lives of hundreds of neonates born with gastroschisis. Since the majority of neonates with gastroschisis typically go on to live a full and normal life, the number of DALYs averted is very high. Gastroschisis has been described as a ‘bellwether procedure’ for neonatal surgery in low-resource settings
^2^. Hence, potentially improving the care for neonates with gastroschisis could also improve outcomes for neonates with other congenital anomalies that require a similar package of neonatal surgical care. This could have a wider global health impact in light of the recent Global Burden of Disease Report findings that congenital anomalies have recently risen to become the fifth-leading cause of death in children under 5 years globally
^136^.

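### ASA score at primary intervention is listed as a confounder, but for models of study period, pre-hospital care or resuscitation it is at least partly a mediator

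*Protocol article*

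**What the plan says.** Under Data analysis, Clinical outcomes, the article gives the purpose of the model: "Multivariate logistic regression analysis will be used to identify factors affecting all-cause in-hospital mortality with adjustment for confounding factors". The next sentence names the candidate covariates: "Potential confounders include gestational age, weight, presence of co-morbidities, and ASA score at the time of primary intervention". The timing of the ASA score is therefore stated.

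Table 1 (Outline of the interventional bundle) lists the core components. The pre-hospital ones include "Covering the bowel in clear plastic • Administering intravenous (IV) fluids • Keeping the neonate warm" and rapid transfer. The in-hospital ones include "Neonatal resuscitation and ward care including IV access, IV fluids, maintenance of normothermia, appropriate antibiotics, regular monitoring and infection control".

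Under Data analysis, Service delivery and implementation outcomes, mortality is also to be regressed on the service delivery outcomes. As listed under Data collection, these include time from birth to arrival, plastic bowel cover on arrival, intravenous fluids before arrival, and time from arrival to primary intervention.

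**The concern.** A confounder must not itself be changed by the exposure. ASA at the primary intervention describes the neonate's condition after referral, transfer and resuscitation, which are stages that the bundle sets out to improve. If a better-prepared neonate has a lower ASA score and therefore a lower risk of death, holding ASA fixed discards that benefit. What remains is at most the effect that does not pass through ASA.

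This matters because the design is a non-randomised before-and-after comparison, and this model is the only analysis described in that section that adjusts for case mix. Under Study impact the article also states: "The study design will enable detailed analysis of which components of the interventional bundle" and of the implementation strategy were and were not effective. Pre-hospital care and resuscitation could be undervalued if ASA is carried into the models that assess them, and the article plans to scale up the intervention if it succeeds.

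**Working it through.** **Step 1: order of events, from the article**

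| Link | Where it stands |
|---|---|
| Condition on arrival is poor | The problem: "neonates commonly arrive hypovolaemic, hypothermic and septic" |
| Pre-hospital components address this and act before arrival | Table 1, core pre-hospital: bowel cover, fluids, warmth, fast transfer |
| Resuscitation comes before bowel reduction | Current practice and guidelines lists, in order, "pre-intervention resuscitation, bowel reduction and defect closure" |
| ASA is scored at the primary intervention | Data analysis, Clinical outcomes |
| ASA at intervention goes with death | Current practice and guidelines links the higher ASA of these neonates to greater peri-operative mortality |

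For these components, and for study period as a summary of the whole bundle, the chain runs from component to condition (ASA) to death. For feeding, later ward care and parenteral nutrition, which act after the primary intervention, ASA comes before the exposure and the chain does not apply. Gestational age, weight and co-morbidities do not have the timing problem.

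**Step 2: the plan's own figure**

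The only power figure is 90% for the unadjusted comparison (Sample size). The arcsine form of the two-sided Z-test is power = Φ(h/√(1/n₁+1/n₂) − 1.96), with h = 2(arcsin√p₁ − arcsin√p₂).

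- 95% to 79%, 67 and 113 patients: h = 0.501, √(1/67+1/113) = 0.1542, so Φ(3.249 − 1.96) = 90.1%.
- 95% to 83%, 109 and 179 patients: h = 0.399, √(1/109+1/179) = 0.1215, so Φ(3.284 − 1.96) = 90.7%.

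The figure reproduces. It does not involve ASA, so nothing in this point changes it.

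**Step 3: how large the attenuation could be (illustration; every ASA input is assumed)**

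The total effects come from the article's rates: (0.79/0.21)/(0.95/0.05) = 0.198 and (0.83/0.17)/(0.95/0.05) = 0.257. The model is logit P(death) = a + d·period + ASA term. The intercept a is solved so that pre-intervention mortality is 95%, then d so that post-intervention mortality is the target. exp(d) is the ASA-adjusted odds ratio.

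*Binary ASA.* High ASA in 80% pre-intervention; log-odds of death +3 for high ASA; mortality 95% to 79%; simulated power of the period term with 67 and 113 patients, 1,000 runs each.

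| High ASA post | Unadjusted OR | Adjusted OR | Power unadjusted | Power adjusted |
|---|---|---|---|---|
| 80% (no change) | 0.20 | 0.12 | 86% | 91% |
| 60% | 0.20 | 0.29 | 83% | 44% |
| 40% | 0.20 | 0.50 | 84% | 8% |

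The fall in power reflects a smaller quantity being tested: the part of the effect that bypasses ASA.

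*Graded ASA.* Grades 2 to 5 at 5/20/50/25% pre and 15/40/35/10% post (full shift), or 10/30/42.5/17.5% post (half shift); log-odds 0.8 to 1.6 per grade. The share removed is 1 − ln(adjusted OR)/ln(total OR).

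| Shift in ASA | Adjusted OR, total 0.198 | Adjusted OR, total 0.257 | Share of log-OR removed |
|---|---|---|---|
| Full | 0.29–0.35 | 0.38–0.49 | 23–47% |
| Half | 0.23–0.24 | 0.31–0.32 | 9–17% |
| None | 0.14–0.18 | 0.19–0.24 | none; moves away from 1 |

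The last row shows non-collapsibility: adjusting for a predictor that does not differ between periods pushes the odds ratio away from 1. The shares in the first two rows therefore mix two opposing effects. Measured against the no-shift odds ratios, the full-shift loss is 27–57%.

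**The case against.** The strongest case on the other side has four parts.

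- **The primary result does not use ASA.** The pre-post mortality comparison is an unadjusted chi-squared or Fisher test, and neither the statistical process control analysis nor the power statement involves a covariate. This stands, and it confines the point to the regression models.
- **The list is open.** The article speaks of potential confounders, does not name study period or any component as a term in the model, and gives no covariates for the service delivery regression. This also stands. The problem arises when one of those exposures enters a model together with ASA. It is still worth settling now, because the article labels a variable measured after these exposures a confounder without restricting where it is used.
- **ASA is a legitimate severity measure for some exposures.** Feeding, later ward care and parenteral nutrition follow the primary intervention, and sicker neonates may be managed differently. A reader might infer that ASA should be deleted from every model. The article does not support that: it would remove severity control where ASA precedes the exposure.
- **The size is unknown.** A reader might infer that pre-hospital care and resuscitation are bound to look ineffective. The article gives no ASA distribution, and with no change in ASA there is no attenuation.

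A reader might also infer that the adjusted model drops neonates who die before any primary intervention, mostly in the earlier period. The article specifies no complete-case analysis and gives no count of such deaths. It also says that included neonates will have all data points completed. That inference cannot be made from what is shown.

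**Conclusion.** The point holds for a defined set of models. For study period, pre-hospital care, resuscitation and the service delivery factors that precede the primary intervention, ASA is at least partly a mediator, and adjusting for it can understate their effect. This follows from the order of care that the article describes. It rests on one assumption: that the bundle improves condition at intervention, which its early components are meant to do.

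The magnitude cannot be derived from the document. The illustrations run from no attenuation to removal of about half the log-odds effect, or slightly more (an odds ratio of 0.50 against 0.20 is 1 − 0.69/1.62 = 57%). The point concerns the interpretation of the adjusted analyses and can be corrected cheaply. It does not undermine the main pre-post test.

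**What to change.** In the Multivariate analysis paragraph, and for the service delivery regression, state the following.

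1. For models of study period, pre-hospital care, resuscitation or upstream service delivery factors, the main adjusted analysis uses only variables that the bundle cannot change (gestational age, weight, co-morbidities and site) and omits ASA at primary intervention.
2. ASA at primary intervention is reported by period as an intermediate outcome.
3. The ASA-adjusted version of those models is presented only as a sensitivity or mediation analysis.
4. ASA may remain as a severity covariate in models of components that act after the primary intervention.

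The cost is a few lines of wording and one extra model, with no new data. The downside is real: ASA also carries baseline severity, so the main model loses some case-mix control. Condition on arrival is no clean substitute, because the pre-hospital component affects it too. Showing the ASA-adjusted model alongside lets readers see how far the conclusion depends on this choice.

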### Service delivery and implementation outcomes

Regression analysis will be undertaken to evaluate the impact of the service delivery outcomes and implementation outcomes including the acceptability (AIM) score, appropriateness (IAM) score, feasibility (FIM) score and fidelity on all-cause in-hospital mortality.

In order to assess sustainability during the post-implementation phase, fidelity of the interventional bundle will be analysed using time series analysis. This will assess whether fidelity remains stable, increases or declines following implementation. Time-series analysis will also be used to assess all-cause in-hospital mortality during the post-implementation phase to determine if there is an upwards, stable or downwards trend following implementation.

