## Abstract

**Background: **Gastroschisis is associated with less than 4% mortality in high-income countries and over 90% mortality in many tertiary paediatric surgery centres across sub-Saharan Africa (SSA). The aim of this trial is to develop, implement and prospectively evaluate an interventional bundle to reduce mortality from gastroschisis in seven tertiary paediatric surgery centres across SSA.

**Methods:** A hybrid type-2 effectiveness-implementation, pre-post study design will be utilised. Using current literature an evidence-based, low-technology interventional bundle has been developed. A systematic review, qualitative study and Delphi process will provide further evidence to optimise the interventional bundle and implementation strategy. The interventional bundle has core components, which will remain consistent across all sites, and adaptable components, which will be determined through in-country co-development meetings. Pre- and post-intervention data will be collected on clinical, service delivery and implementation outcomes for 2-years at each site. The primary clinical outcome will be all-cause, in-hospital mortality. Secondary outcomes include the occurrence of a major complication, length of hospital stay and time to full enteral feeds. Service delivery outcomes include time to hospital and primary intervention, and adherence to the pre-hospital and in-hospital protocols.  Implementation outcomes are acceptability, adoption, appropriateness, feasibility, fidelity, coverage, cost and sustainability.

Pre- and post-intervention clinical outcomes will be compared using Chi-squared analysis, unpaired t-test and/or Mann-Whitney
*U *test. Time-series analysis will be undertaken using Statistical Process Control to identify significant trends and shifts in outcome overtime. Multivariate logistic regression analysis will be used to identify clinical and implementation factors affecting outcome with adjustment for confounders.

**Outcome: **This will be the first multi-centre interventional study to our knowledge aimed at reducing mortality from gastroschisis in low-resource settings. If successful, detailed evaluation of both the clinical and implementation components of the study will allow sustainability in the study sites and further scale-up.

**Registration: **ClinicalTrials.gov Identifier
NCT03724214.

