The method of dissemination and implementation of the pre-hospital management protocol will vary at each centre according to the optimal strategy as determined by the local team. Strategies include: • Wide dissemination of a guideline, leaflet and poster detailing the protocol with pictorial representations of the steps involved via post +/- back-up with telephone communications. • In addition to the above, site visits to selected referral centres for education and training to enhance implementation of the protocol. Visits and training will be undertaken by local MDT members and the principal investigator. • As an alternative to visiting referral hospitals, a gastroschisis study day at the study centre with MDT members from referral hospitals invited for education and training to enhance implementation of the protocol. • Dissemination of the protocol through existing government health policy pathways. • Radio and/or television campaign.	• Administration of a short period of parenteral nutrition for neonates who have survived to 7-days of life. • Maternal involvement in monitoring and basic management. • Management of neonates with gastroschisis on the neonatal ICU if available.

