### Service delivery outcomes

1)   Time from birth to arrival at the study centre (hours).

2)   Proportion of patients with clear plastic bowel coverage at the time of arrival to the study centre.

3)   Proportion of patients with intravenous fluids prior to arrival at the study centre.

4)   Time from arrival to primary intervention (hours).

5)   Number and position of MDT members present during the initial resuscitation, primary intervention and defect closure.

6)   Proportion of patients receiving PN at some point during their hospital stay.

All patient data will be collected prospectively using
REDCap Data Capture Software
^128^. Data collection forms will be printed for real-time data collection at the patient’s bedside. This can be uploaded later to REDCap. Patient data entered into REDCap will be anonymous and local study teams will maintain a spreadsheet to keep track of REDCap IDs alongside the patient identifiable information. A pilot study was undertaken to ensure the data collection form is usable, appropriately worded and contains all the relevant content prior to project launch.

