### Implementation outcomes

***Acceptability, adoption, appropriateness and feasibility.*** These will be evaluated and addressed during the qualitative studies, Delphi process and in-country co-development meeting to optimise the interventional bundle prior to implementation. Definitions are documented in the introduction section above. In order to evaluate these outcomes post-intervention, MDT members and parents will be invited to undertake a validated 12-item survey on acceptability, appropriateness and feasibility during the 4
^th^ week of the in-country implementation phase and again at the end of the study (
Supplementary File 6)
^110,
129^.

***Fidelity.*** The proportion of management protocol components completed as intended will be assessed using a checklist at the time of preformed silo application and defect closure. The checklist will be completed by the person undertaking the intervention for every neonate included in the study. A second observer, who has been trained in the gastroschisis management protocol, will independently complete the checklist for 50% of the cases.

Fidelity of the implementation process will also be evaluated as follows:

1)   Number of centres where the study leads inputted into the study design and protocol either via video conference with the PI and/or via internet communications.

2)   Total number and position of the MDT members* engaged in the qualitative study and/ or Delphi process from each study site.

3)   Did an in-person co-development meeting take place at the start of the implementation phase at each study site (yes/no).

   If yes, were adaptations made to the interventional bundle accordingly (yes/no).

   If yes, how many of each of the MDT members
^4^ were present during the meeting.

1)   Total number and position of the MDT members completing the MDT training day.

2)   Proportion of referral hospitals
^5^ (as identified by the study leads at each centre) receiving implementation of the pre-hospital management protocol through in-person education and training.

In order to accurately evaluate fidelity of both the interventional bundle and implementation process it will be important to distinguish between non-compliance and purposive adaptations
^130,
131^. Stirman
*et al*. have produced a framework and coding system for adaptations of evidence-based interventions that will be used to accurately document any deviations from the original plan at each site throughout the duration of the study

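### Regressing in-hospital mortality on receipt of parenteral nutrition at any time builds in immortal-time bias towards benefit; for fidelity the bias depends on how unreached closure items are scored

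*Protocol article*

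**What the plan says.** Under Data analysis, Service delivery and implementation outcomes, the protocol article states: "Regression analysis will be undertaken to evaluate the impact of the service delivery outcomes and implementation outcomes". The outcome of that regression is all-cause in-hospital mortality, and the named implementation predictors end with "feasibility (FIM) score and fidelity on all-cause in-hospital mortality". The service delivery outcomes are listed under Data collection; the sixth is "Proportion of patients receiving PN at some point during their hospital stay". The model type comes from the Abstract: "Multivariate logistic regression analysis will be used to identify clinical and implementation factors affecting outcome with adjustment for confounders". The multivariate analysis paragraph under Data analysis also names logistic regression for in-hospital mortality.

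Two other places fix the timing. Table 1 lists as an adaptable in-hospital component: "Administration of a short period of parenteral nutrition for neonates who have survived to 7-days of life". The Introduction (The problem) describes most neonates with gastroschisis in low- and middle-income countries, simple and complex together, as "dying within a median of 4-days at a healthcare facility".

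Fidelity is the proportion of protocol components carried out as intended. It "will be assessed using a checklist at the time of preformed silo application and defect closure", for every included neonate. The number and position of team members present is also recorded at resuscitation, primary intervention and closure.

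**The concern.** A neonate can receive the bundle's PN only after surviving to day 7. If the typical death comes earlier, most deaths occur before PN is possible, and each of them enters an ever/never comparison as an untreated death. The PN group, by contrast, has a guaranteed death-free first week. Adjustment for gestational age, weight, co-morbidities and ASA score cannot remove this, because the distortion comes from how exposure is defined and not from case mix.

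The Study impact section says the design will show which components of the bundle worked, and it looks ahead to scale-up. PN is chosen site by site and needs infrastructure that the article lists as a barrier. A large artefactual benefit could therefore influence what is adopted and paid for elsewhere.

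**Working it through.** The article gives no figure for this regression, so there is no stated value to reproduce. The size of the bias can be derived.

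**Inputs from the article:** PN possible from day 7 (Table 1); median 4 days to death (Introduction); 79% post-intervention mortality with 113 neonates, or 83% with 179 (Sample size).

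**Assumptions not in the article:** exponential death times among those who die; PN with no effect, given at random to a share u of neonates alive at day 7; time since admission equal to age.

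**Derivation.** Let M be mortality and f the share of deaths after day 7, so f = 2^(-7/median).
- Odds of death with PN: Mf / (1 − M).
- Odds of death without PN: M(1 − uf) / [(1 − M)(1 − u)].
- Ratio: OR = f(1 − u) / (1 − uf). M cancels, so the bias does not depend on overall mortality.

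**Central case (median 4 days, u = 0.5, M = 0.79).**
- f = 2^(-1.75) = 0.297.
- Alive at day 7: 0.21 + 0.79 × 0.297 = 0.445.
- Mortality with PN: 0.79 × 0.297 / 0.445 = 0.528.
- Mortality without PN: (0.79 − 0.5 × 0.445 × 0.528) / (1 − 0.5 × 0.445) = 0.865.
- OR = 0.297 × 0.5 / (1 − 0.1486) = 0.175.

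**Range.**

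| Median to death | Uptake u | f | Spurious OR |
|---|---|---|---|
| 3 days | 80% | 0.198 | 0.047 |
| 3 days | 50% | 0.198 | 0.11 |
| 4 days | 50% | 0.297 | 0.175 |
| 5 days | 50% | 0.379 | 0.234 |
| 4 days | 20% | 0.297 | 0.253 |
| 10 days | 50% | 0.616 | 0.445 |

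The two time scales also differ: the median counts days at a facility, whereas eligibility counts days of life. A neonate admitted at one day of age needs six facility days to become eligible. Then f = 2^(-6/4) = 0.354 and, at u = 0.5, OR = 0.177 / 0.823 = 0.21. If some PN starts earlier than the bundle rule, for example before the intervention, the OR at a 4-day median and 50% uptake is 0.33 for a day-4 start and 0.55 for a day-2 start.

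**Simulation (2,000 logistic fits per setting, central-case timing and uptake).** An ineffective PN programme reached p < 0.05 in 92% of runs with 113 neonates at 79% mortality, and in 98% with 179 at 83%. Restricted to neonates alive at day 7, the median OR was 1.00, with false-positive rates of 4.6% and 4.0%.

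**Fidelity.** The same simulations assumed closure at day 5, ten silo and ten closure items, 80% completion and no effect on death.
- Closure items scored as not completed for neonates dead before closure: OR 0.51 to 0.52 per 10 percentage points, significant in every run.
- Only neonates who reached closure analysed: OR 0.99 to 1.00, significant in 4–5%.
- Silo items only, among neonates who reached silo application: OR 0.99 to 1.00, significant in 4%.

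**The case against.** A reader might infer that every predictor recorded after admission will show a false protective effect. The article does not support that. If neonates who die before closure have no closure record, they are missing from a closure-stage analysis, not scored low. The simulation then shows no false slope. A scoring rule that turns unreached items into failures would create the bias, but the Fidelity paragraph does not state one. Team presence at closure and time to primary intervention likewise have absent values for early deaths, and no bias has been computed for either. The staff survey scores, bowel coverage on arrival, fluids before arrival and time from birth to arrival do not depend on in-hospital survival at all.

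For PN there are fair reservations:
- The regression sentence does not name PN. It enters as one of the service delivery outcomes, and the ever/never coding is inferred from its definition.
- The 4-day median comes from earlier cohorts that included complex cases, which this study excludes, and the bundle may itself delay deaths.
- Uptake is unknown. PN is optional, and the Introduction reports access in only 19% of surveyed low-income-country centres.
- PN given preferentially to sicker neonates would push the other way.

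These points widen the range and temper certainty about the net result. Later deaths and lower uptake still leave the spurious OR well below 1, and the only PN definition the article gives is receipt at any time.

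**Conclusion.** The point holds for PN. Followed as written, the regression compares neonates who had to survive a week with a group that contains nearly all the early deaths. With no true effect, the spurious OR is about 0.17 under the central assumptions and roughly 0.05 to 0.45 over the range of medians (3 to 10 days) and uptakes (20% to 80%) considered. Those figures rest on exponential death times and on PN being unrelated to severity; selection of sicker neonates for PN could offset part of the bias.

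For fidelity the problem is conditional on how unreached closure items are handled. It should be closed off by wording, not reported as an established bias.

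A reader might also infer that the main mortality result is compromised. It is not: the primary comparison is by period, and PN and fidelity do not enter it. The affected analysis is explanatory, so this is a correction that should be made and not one on which the study's validity depends.

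**What to change.** 1. State that the association of PN with mortality will be estimated only among neonates alive at day 7, by PN status fixed at the landmark or by a clearly defined start window after it. Alternatively, if PN start dates are recorded, treat PN as a time-dependent exposure and live discharge as a competing event. The data collection form is not shown, so availability of start dates needs checking.
2. State that an ever/never PN coefficient from the whole cohort will not be interpreted.
3. Use silo-application items as the fidelity predictor in the mortality model, among neonates who reach silo application. Analyse closure-stage items and team presence at closure only among neonates who reach closure, and never score unreached closure items as not completed.

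The landmark version changes the analysis wording, not the design. Its price is a smaller set: at 79% mortality the share alive at day 7 is 0.21 + 0.79 × 0.198 = 37% for a 3-day median and 0.21 + 0.79 × 0.379 = 51% for a 5-day median. That is about 41 to 58 of the minimum 113 post-intervention neonates, so the PN estimate will be imprecise and should be reported with its confidence interval.
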